### General procedure and monitoring

2.5

#### Data collection and management

2.5.1

At enrolment, the investigators will collect data on the participants’ socioeconomic status, education, and obstetric history, duration of HIV diagnosis (in months), WHO clinical stage of the disease,^[22]^ type and duration of ART use (in months), baseline Haemoglobin (Hb) levels (in g/dL), CD4 + cells count (in cells/mm^3^) and viral load (in copies/mL), and BMI (actual maternal weight is calculated by subtracting the estimated fetal weight at enrolment using a normogram chart from the measured maternal weight) (in kg/m^2^) using a structured interviewer-administered questionnaire. Gestational age is based on the date of the participant's last menstrual period, which will be obtained at the time of random assignment. Data collection begins on the day a participant is allocated into an intervention arm and continues until the termination of the trial or until the participant withdraws from the trial at any time for any reason. At delivery, data will be collected from the participants’ case notes on the latest CD4 + cells count and viral load (done within the last 6 weeks of delivery), WHO stage of the disease, and latest Hb levels. The total duration of supplement intake – selenium or placebo (in weeks), level of compliance to use of the supplement (good compliance level is defined as usage of at least 10 of the 16, 2-weekly prescribed tablets), mode of delivery, gestational age at delivery (in weeks) and the baby's birth weight (in grams) will also be recorded in the questionnaire. Original data will be transferred to an electronic database system located in a guarded facility at the trial site by the research assistant. Access to the study data is restricted. The PI will have the access to the final dataset. An independent steering committee will monitor and examine strict compliance with the study protocol (Fig. 1 and Table 1). Trial progression or protocol modification will be updated in the registered database (Pan African Clinical Trial Registry, PACTR) and reported to the LUTH's ethical committee that will provide the oversight functions of data and safety monitoring in the course of the study.

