### Study population/ participant enrolment

2.2

Eligible participants are confirmed HIV-seropositive pregnant women aged 15 to 49 years who have a singleton gestation at 14 to 27 weeks’ gestation. The exclusion criteria at enrolment are multiple gestations, significant renal and hepatic impairment, an expected delivery date beyond March 2019, receipt of a long course of mineral supplement containing selenium during the 6 months prior to enrolment, refusal of consent at enrolment or withdrawal of consent during the study.

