### Confirmatory outcome variables

2.6

Primary endpoints – Preterm birth (delivery before 37 completed weeks of pregnancy) and low birth weight in term neonates (baby's birth weight less than 2.5 kg).

Secondary endpoints – HIV disease progression (change in CD4 + cells count, viral load and stage of the disease); mid-trimester miscarriage, change in haemoglobin levels; adverse events (AE) such as hepatotoxicity, gastrointestinal disturbances, dermatologic effects (nail and hair loss and dermatitis), and neurotoxicity; and perinatal mortality (number of stillbirths and neonatal deaths in the first week of life).

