#### Sample size

2.7.1

Using the data from our previous study,^[11]^ we propose to enrol 148 participants in the study to investigate the effect of selenium supplementation on the primary endpoints. The study is powered for a 2-sided test with a Type I error rate of 5% and 95% power, that is, Z_α_ = 1.96 and Z_β_ = 1.64, adjusted for a 20% drop-out rate. We also propose to enrol 180 participants to detect an effect size of 0.3 of selenium supplementation on the major secondary endpoint (reduction in HIV disease progression). This is powered for a 2-sided test with a Type I error rate of 5% and 80% power, that is, Z_α_ = 1.96 and Z_β_ = 1.64, adjusted for a 20% drop-out rate. Therefore, a total sample size of 180 is used in this study with 90 HIV-infected women randomised into each of the trial arms to assess the effects of selenium supplementation on the primary and secondary outcome variables.

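### Both primary endpoints rest on a menstrual date obtained at 14 to 27 weeks with no stated confirmation; dating error risks diluting them, and the sample size allows only for drop-out

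*Protocol article*

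**What the plan says.** The rule is in the protocol article, section 2.5.1 (Data collection and management): gestational age is taken from the date of the "last menstrual period, which will be obtained at the time of random assignment". Section 2.2 places enrolment at a "singleton gestation at 14 to 27 weeks’ gestation", so the date is obtained more than three months after the event it records.

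Section 2.6 defines the primary endpoints as "Preterm birth (delivery before 37 completed weeks of pregnancy) and low birth weight in term neonates (baby's birth weight less than 2.5 kg"). At birth, "gestational age at delivery (in weeks) and the baby's birth weight (in grams) will also be recorded in the questionnaire".

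The visible text mentions no ultrasound dating, no redating rule and no handling of an uncertain menstrual date. Section 2.3 has eligible women invited to consent within 2 weeks of screening, which already requires a gestational age. It does not say whether that age and the one fixed at randomisation come from the same source.

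On size, section 2.7.1 says "we propose to enrol 148 participants in the study to investigate the effect of selenium supplementation on the primary endpoints", at 95% power, two-sided 5%, with 20% drop-out. It then enrols 180 because of the main secondary endpoint. It gives no event rates and no effect size for the primary endpoints.

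**The concern.** One measurement carries three decisions: who is eligible, who delivered preterm, and which neonates enter the low-birth-weight comparison. An error of a week or two in the menstrual date moves births near 37 weeks across the threshold in either direction. For preterm birth, error that is alike in both arms shrinks the observed risk difference and usually costs power. For the second endpoint, misdated preterm babies enter the term group and misdated term babies leave it, so the comparison is no longer made in the population that the protocol names.

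What is at stake is a real benefit being missed or understated. This is a dating rule that the protocol states, not a detail it leaves open, so following it as written carries the risk.

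**Working it through.** **Inputs from the protocol.** 148 enrolled for the primary endpoints; 95% power; two-sided 5%; 20% drop-out; 180 enrolled in the end, 90 per arm (section 2.7.1).

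**Inputs that are assumptions.** Control preterm rates of 25% to 50%, and the sensitivity (Se) and specificity (Sp) of the menstrual date for birth before 37 weeks. The protocol gives none of these.

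**Step 1: the plan's own figure.** 148 × 0.8 = 118, or 59 evaluable per arm. Without event rates the 148 can be neither reproduced nor refuted. I therefore solved for the treated rate that gives 95% power at n = 59 per arm, using

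power = Φ{ [ |p1 − p2| − 1.96·√(2p̄(1 − p̄)/n) ] / √[ (p1(1 − p1) + p2(1 − p2))/n ] }.

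For p1 = 25% this gives p2 = 2.65%: (0.2235 − 1.96 × 0.0636)/0.0601 = 1.645, so 95.0%.

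**Step 2: credit the actual enrolment.** 180 × 0.8 = 144, or 72 per arm. For the same effect, (0.2235 − 1.96 × 0.0575)/0.0544 = 2.03, so power is 98% with perfect dating.

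**Step 3: add dating error, equal in both arms.** Observed rate = Se·p + (1 − Sp)(1 − p). The risk difference is multiplied by Se + Sp − 1, which is 0.92, 0.85 and 0.77 for the three pairs below, a shrinkage of 8%, 15% and 23%.

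Example at 0.90/0.95:
- control: 0.90 × 0.25 + 0.05 × 0.75 = 26.25%
- treated: 0.90 × 0.0265 + 0.05 × 0.9735 = 7.3%
- power at 72 per arm: 87%

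Power at 72 per arm, with 59 per arm in brackets:

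| Control vs treated | Perfect dating | 0.95/0.97 | 0.90/0.95 | 0.85/0.92 |
|---|---|---|---|---|
| 25% vs 2.7% | 98% (95%) | 93% (88%) | 87% (80%) | 76% (67%) |
| 30% vs 5.3% | 98% (95%) | 94% (89%) | 89% (82%) | 80% (71%) |
| 40% vs 11.7% | 98% (95%) | 95% (90%) | 91% (85%) | 84% (76%) |
| 50% vs 19.2% | 98% (95%) | 95% (91%) | 92% (86%) | 86% (78%) |

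**Step 4: a second model, in weeks.** Take gestational age at delivery as normal (SD 2 to 2.5 weeks) with independent menstrual-date error. For the same control rates at 72 per arm, an error SD of 0.5 week leaves 97-98% power, 1 week 95-98%, 2 weeks 82-96% and 3 weeks 62-91%. At a 20% control rate (vs 0.4%) this model hardly lowers power, because the error also raises the observed event rates.

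These figures are for preterm birth. I did not quantify the term low-birth-weight endpoint. That would also need birth-weight rates in misdated babies, and babies wrongly counted as term could carry part of any preterm effect into it.

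**The case against.** The strongest objection is that a loss of power cannot be shown. A reader might infer that preterm birth is in fact misclassified and that the stated 95% power is not delivered. The documents do not support this: they give no dating accuracy, event rates or effect size. The 95% also belongs to 148 women, not to the 180 enrolled. If 95% is pegged to 72 per arm instead (25% vs 4.2%), the three error cases give 88%, 81% and 69%. That reading discards the surplus the trial actually has. This objection stands, and the figures above start from 148 for that reason.

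The text says that gestational age is based on the menstrual date. It does not say that the date is unaided recall, that it is the sole source, or that uncertain dates are accepted. Table 1 and Figure 1 are not visible, and the article condenses a fuller protocol that may hold a redating rule. This also stands, and it limits the point to what the visible text states. It does not remove the point, because a specific rule is given and no check is attached to it.

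The Se/Sp pairs are not derived from an error in weeks, and the direct model in Step 4 is kinder: an SD of 1 week costs almost nothing. That is correct, but an SD of 2 weeks can still take power to 82%.

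A reader might also fear a false-positive result. Randomisation and blinding (section 2.3) make the error similar in both arms, so dilution is the concern.

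Finally, no section mentions a scan. Multiple gestations are excluded without saying how that is established, so a scan on file is plausible but not assured.

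**Conclusion.** The point holds as a risk of unknown size. Both primary endpoints and the eligibility window depend on a menstrual date obtained at 14 to 27 weeks, with no confirmation in the visible text, and the sample size allows for drop-out alone. With the effect set to 95% power at 148 enrolled and control rates of 25% to 50%, the 180 enrolled start at 98% power for preterm birth. They keep 93-95% under small dating error, 87-92% under moderate error and 76-86% under larger error. The margin from 148 to 180 thus absorbs small error but not moderate error.

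This rests on assumed event rates, assumed dating accuracy, error that is equal across arms, and 20% loss. It is a worthwhile and cheap improvement. It does not show that the trial is underpowered.

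**What to change.** Section 3.1 reports that recruitment had not begun. Before enrolment starts, replace the dating sentence in section 2.5.1 with a fixed rule applied blind to arm:

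- Where the case notes hold a dating scan done before randomisation, use the earliest one if it differs from the menstrual date by more than a pre-stated number of days. Otherwise use the menstrual date.
- Record for every woman the dating source and whether the menstrual date is certain.
- Repeat both primary analyses in women with a scan or a certain date, as a sensitivity analysis.

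Limiting the rule to scans done before randomisation keeps the dating independent of treatment.

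The cost is a change of wording and one or two extra data fields. No new scans are needed, and case notes are already reviewed at delivery. The limitation is that women without a scan on file keep the weaker dating, so the gain depends on how many have one. Some women's eligibility dating may also shift under the rule, which is another reason to settle it before the first woman is randomised.

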### Study design and setting

2.1

The study is designed as a prospective, randomized, double-blind, placebo-controlled, single-center trial involving confirmed HIV-seropositive pregnant women who are seeking care at the antenatal clinics of the Lagos University Teaching Hospital (LUTH). LUTH is the teaching hospital of the College of Medicine, University of Lagos. It has more than 1000 beds and is located in the metropolis of Lagos in Southwest Nigeria. The hospital provides services to patients from the neighbouring states in Southwest Nigeria. It is the largest hospital in Lagos State and mainly offers clinical services, including prenatal, intrapartum, and postnatal care. Pregnant women with HIV infections are jointly managed by haematologists and HIV physicians at the hospital's AIDS Prevention Initiative Nigeria (APIN) clinic and undergo regular monitoring of their disease with 3-monthly CD4+ cells count and viral load. Participants’ enrolment will start in September 2018, and the last woman is expected to be included in the trial in February 2019. The Health Research and Ethics Committee of LUTH's Institutional Review Board has granted ethics approval for this study (Approval Number ADM/DCST/HREC/APP/2438; 30th August 2018).

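### End-of-study CD4 count and viral load come from case notes within a 6-week window, but the routine testing described is 3-monthly: unless a test is scheduled in the window, roughly half the women are expected to lack these values

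*Protocol article*

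**What the plan says.** Section 2.1 says that pregnant women with HIV at the hospital's clinic "undergo regular monitoring of their disease with 3-monthly CD4+ cells count and viral load". Section 2.5.1 sets the source of the end-of-study data: "At delivery, data will be collected from the participants’ case notes". The CD4 and viral load item is the "latest CD4 + cells count and viral load (done within the last 6 weeks of delivery"; WHO stage and haemoglobin follow in the same list without a time limit. Baseline CD4 and viral load are recorded at enrolment, with no test date or window given.

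Section 2.2 admits women "who have a singleton gestation at 14 to 27 weeks’ gestation". Section 2.6 defines the secondary endpoint as "HIV disease progression (change in CD4 + cells count, viral load and stage of the disease". Section 2.7.1 proposes to "enrol 180 participants to detect an effect size of 0.3 of selenium supplementation on the major secondary endpoint (reduction in HIV disease progression", and this figure, not the 148 for the primary endpoints, sets the total. The allowance for loss is 20%.

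The visible text describes no trial-specific CD4 or viral load test near delivery and no rule for a latest result older than 6 weeks. Table 1, the schedule of assessments, is not shown.

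**The concern.** The window is shorter than the interval between the tests that are meant to fill it. A woman has an in-window result only if one of her routine tests happens to fall in the last 6 weeks before delivery. For the rest, staff must either leave the item blank or enter an older result that the text does not cover.

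Two things are at stake. The first is the amount of data on the endpoint that fixed the sample size. The second is which women contribute: if test dates follow enrolment, having a value can depend on gestational age at delivery. Preterm birth is a primary endpoint that selenium may itself affect, so a complete-case comparison could then select on a post-randomisation outcome.

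**Working it through.** **The plan's own figure.** Section 2.7.1 gives an effect size of 0.3, Zα = 1.96, Zβ = 1.64 and 20% drop-out. (1.96 + 1.64)² / 0.3² = 144.0, and 144 / 0.8 = 180. The stated total reproduces, but from a one-sample formula and the Zβ for 95% power, although the text says 80%. A two-arm comparison at 80% power needs 175 per arm, or 350 / 0.8 = 438 in total. That is a separate problem, but it sets the starting point for power below.

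**Inputs for coverage.**
- Window: 6 weeks (section 2.5.1), read as the weeks up to delivery because collection is at delivery.
- Test interval: 3 months (section 2.1), taken as 13 weeks.
- Enrolment: 14 to 27 weeks (section 2.2).
- Assumption: no extra trial test, and test dates either (a) random relative to delivery, or (b) at enrolment and every 13 weeks after.

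**Share with an in-window value.** Under (a), 6/13 = 46%, so 54% lack one (50% if 3 months is 12 weeks). That is 180 × 7/13 = 97 women, or 144 × 7/13 = 78 of those left after 20% drop-out. Under (b) with enrolment uniform over 14 to 27 weeks, simulation also gives 46%. Mean delivery age of 37 to 40 weeks, or 2-week jitter in test dates, leaves it at 45 to 46%. If enrolment clusters, coverage under (b) is 22% (all at 14 to 20 weeks) to 67% (all at 20 to 27 weeks), so 33% to 78% lack a value.

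**Dependence on delivery date, under (b).**
- Uniform enrolment: coverage is the same 6/13 for deliveries at 33, 34, 36, 38 or 40 weeks, and drops only before 33 weeks.
- Late enrolment (uniform over 20 to 27 weeks): the first routine test falls at 33 to 40 weeks. For delivery at 36 weeks, tests at 33 to 36 count: 3/7 = 43%. For delivery at 39 weeks, tests at 33 to 39 count: 6/7 = 86%.
- Early enrolment (uniform over 14 to 20 weeks): tests fall at 27 to 33 and 40 to 46 weeks. For delivery at 36 weeks, tests at 30 to 33 count: 3/6 = 50%. For delivery at 39 weeks, the window of 33 to 39 contains none: 0%.

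A link with delivery timing therefore appears when enrolment is skewed, and its direction depends on the skew.

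**Power.** Two-sample t test, two-sided 5%, taking 0.3 as a standardised mean difference on a continuous component:

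| Women per arm | Source | Power |
|---|---|---|
| 90 | all randomised | 52% |
| 72 | after 20% drop-out | 43% |
| 42 | 90 × 6/13 | 27% |
| 33 | 72 × 6/13 | 22% |

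**Using all post-baseline tests, under (b).** A woman has at least one if she enrolled 13 or more weeks before delivery. For delivery at 36 weeks this means enrolment by 23 weeks: 9/13 = 69%. For delivery at 38 weeks it means enrolment by 25 weeks: 11/13 = 85%. Averaged over delivery dates (mean 38.5 weeks, SD 2), simulation gives about 86%, against 46% in window.

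**The case against.** The strongest reply is that the key premise is unseen. Table 1 is where a trial test near delivery would be listed, and the parenthesis in section 2.5.1 can be read as saying that such a test is done and then transcribed. Section 2.1 describes regular monitoring and does not exclude further tests; section 2.5.1 does not declare older results invalid. This stands, and it makes the conclusion conditional. It does not remove the need to reconcile the two sections, because the source as written is the case notes and the only testing frequency given is 3-monthly.

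A reader might infer that half the women will have no value for the major secondary endpoint at all. The text does not support that: WHO stage is one of three components and has no window.

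A reader might also infer that missing values are inherently tied to preterm birth. With random test dates, or uniform enrolment, coverage is 46% whatever the delivery week from 33 on. The link needs skewed enrolment. The limit on expected delivery date in section 2.2 may push enrolment later, but the actual distribution is unknown.

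Nor is the low power due to the window alone: it is already 43% at 72 per arm with complete data. The last row of the table also applies the window loss on top of the full 20% drop-out.

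A window on both sides of delivery would cover 92%, but collection at delivery argues against that reading.

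**Conclusion.** The concern holds in conditional form. If no test is scheduled in the last 6 weeks, about half the women (54% at a 13-week interval; 33% to 78% with clustered enrolment) are expected to lack an in-window CD4 count and viral load. Even the favourable end of that range exceeds the 20% allowed for, and it comes on top of drop-out. For those two components, power for an effect of 0.3 would roughly halve, from about 43% to about 22%. Selection by gestational age at delivery is an added risk only if enrolment is skewed early or late.

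The central figure rests on assumed test dates, not on a figure in the article. A scheduled in-window test in Table 1 would largely settle the point.

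**What to change.** Reconcile sections 2.1 and 2.5.1: state whether a CD4 and viral load test is scheduled in the last 6 weeks, and what is recorded when the latest result is older.

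In section 2.5.1, drop the 6-week restriction and record every routine post-baseline CD4 count and viral load up to delivery, each with its test date. In section 2.8, analyse CD4 and log10 viral load in a model with baseline value, arm and weeks since randomisation, such as a mixed model. The tests now listed there do not make use of repeated values. Keep the in-window value as a sensitivity analysis.

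The cost is wording, extraction of dated results from the same notes, and a somewhat more complex model; no new tests are needed. In the enrolment-anchored case, coverage rises from about 46% to about 86%.

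There are downsides. Values come at varying times before delivery, some after little exposure to the supplement. Women who enrol late and deliver early may still have no post-baseline test: about 14% overall under anchored tests and uniform enrolment, 31% of those delivering at 36 weeks and 15% at 38 weeks. Their number should be reported by arm. The change does not repair the sample size, which is too small for the stated power even with complete data.

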**Figure 1 F1:**
[figure not shown]
Trial flow chart.

**Table 1 T1:**
[figure not shown]
Schedule of enrolment, interventions, and outcome assessments in the trial.

### Confirmatory outcome variables

2.6

Primary endpoints – Preterm birth (delivery before 37 completed weeks of pregnancy) and low birth weight in term neonates (baby's birth weight less than 2.5 kg).

Secondary endpoints – HIV disease progression (change in CD4 + cells count, viral load and stage of the disease); mid-trimester miscarriage, change in haemoglobin levels; adverse events (AE) such as hepatotoxicity, gastrointestinal disturbances, dermatologic effects (nail and hair loss and dermatitis), and neurotoxicity; and perinatal mortality (number of stillbirths and neonatal deaths in the first week of life).

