## Introduction

1

Micronutrient deficiencies are common during pregnancy, especially in pregnant women from economically disadvantaged settings where diets with low content of minerals and vitamins are consumed.^[1]^ Selenium is a non-metallic chemical element of great importance to human health.^[2,3]^ It is a key component of several human seleno-proteins and mostly involved in redox reactions.^[4]^ It acts as an antioxidant and helps protect the body against the damaging effects of free radicals.^[5]^ Selenium is essential for the activity of the enzyme glutathione peroxidase (GPX), a main intracellular antioxidant that protects against reactive oxygen species and subsequent oxidation-induced cellular damage.^[5,6]^ Biochemical selenium deficiency has been associated with increased mortality among those infected with HIV^[7]^ and with accelerated HIV disease progression through increased viral load.^[8]^ Selenium's role in antioxidant defence^[9]^ and immunity^[10]^ may be the underlying mechanism. There is, however, limited data on the selenium status of Nigerian pregnant women with HIV-infection, with a recent study conducted by us showing a prevalence rate of selenium deficiency to be 20.4% and we reported significantly increased rates of preterm birth and delivery low birth weight babies among the HIV infected participants with selenium deficiency.^[11]^ Several other studies have also reported low selenium status in HIV-infected individuals, and that serum selenium concentration declines with disease progression.^[12,13]^

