Selenium is found in cereals, meat, poultry, seafood, and eggs.^[6]^ Cereals may provide about 50% of dietary selenium, however data on the selenium content of Nigerian or African foods is also limited. The selenium content of plant foods varies with the selenium content of the soil.^[6]^ The Recommended Dietary Intake of selenium for pregnant women is 60 mg/day^[6]^ and most interventional studies make use of daily doses of up to 200 μg selenium in its elemental form (selenomethionine).^[14–17]^ Supplemental doses up to 200 μg of the mineral should not cause adverse effects, even if temporarily exceeded, since the selenium upper tolerable intake (UL) for this group is established as 400 μg (5.1 μmol) selenium/day.^[18]^ Given the high UL and the regulation of body homeostasis through urinary excretion, selenium supplementation can be regarded as a safe intervention.^[18,19]^ There is still limited data about selenium toxicity in humans, but the most common side effects include: hair and nail brittleness and loss, gastrointestinal disturbances, skin rash, fatigue, irritability and nervous system disturbances.^[6,19]^ Selenium containing supplements are not recommended for children under the age of 15 years.^[6]^ There is currently paucity of studies that examined the effects of selenium supplementation among pregnant HIV-infected black African women. This study will therefore attempt to assess the effect of antenatal selenium supplementation on major pregnancy outcomes (preterm birth and low birth weight) and HIV disease progression rate among pregnant women at the Lagos University Teaching Hospital (LUTH), Lagos, Nigeria.

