### Statistical analyses

2.8

The intention-to-treat principle will be used in the final analyses. Statistical analyses will be carried out using SPSS version 23.0 for Windows (Armonk, NY: IBM Corp.). The associations between any 2 groups of continuous variables will be tested using the independent sample or paired *t* test (normal distribution) or the Mann-Whitney *U* test (skewed data) and that of 2 groups of categorical variables with chi-square or Fishers exact test where appropriate. A series of multivariable analyses using binary logistic regression model will also be carried out to identify and control for several possible confounders of the primary and secondary outcome variables. Statistical significance will be defined as *P* < .05.

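### The second primary endpoint counts low birth weight in term neonates only, so it selects on the other primary endpoint after randomisation; if selenium reduces preterm birth, the comparison can be biased against it

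*Protocol article*

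**What the plan says.** Section 2.6 (Confirmatory outcome variables) lists two primary endpoints. The first is "Preterm birth (delivery before 37 completed weeks of pregnancy"). The second is "low birth weight in term neonates", with the cut-off set at 2.5 kg.

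Four other places bear on the second endpoint:

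- The aim at the end of the Introduction is to assess the "effect of antenatal selenium supplementation on major pregnancy outcomes (preterm birth and low birth weight"). It has no term restriction.
- The Introduction says the earlier study, which section 2.7.1 uses for sizing, found "significantly increased rates of preterm birth and delivery low birth weight babies". That description has no term restriction either.
- Section 2.2 admits women with a "singleton gestation at 14 to 27 weeks" of gestation, so nobody's term status is known at randomisation.
- Section 2.8 states: "The intention-to-treat principle will be used in the final analyses".

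The article does not say how preterm births enter the second endpoint, and it does not mention the selection that the restriction creates.

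**The concern.** Randomisation makes the two arms comparable at 14 to 27 weeks. It does not make comparable two subsets chosen by something that happens later and that the treatment is meant to change. Being born at term is exactly that: it is the complement of the first primary endpoint.

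If selenium prevents some preterm births, those babies enter the term group in the selenium arm. Their counterparts in the placebo arm are born preterm and are left out. Babies only just moved past 37 weeks may well be lighter than other term babies. In that case the selenium arm's term group contains more small babies although none is worse off.

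The reading of a confirmatory endpoint is at stake. A real benefit on prematurity could appear as no effect, or as an adverse effect, on term LBW. Separately, the endpoint does not answer the question the Introduction poses, because LBW babies born preterm do not count in it.

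**Working it through.** The article gives no preterm or LBW rates, so it has no figure of its own to reproduce. All rates below are assumptions; the arm size and drop-out rate come from section 2.7.1.

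**Notation.** pc and pt are the preterm risks on placebo and selenium, with pt < pc. q is the LBW risk in babies who would be term in either arm. r is the LBW risk, once born at term, in babies moved from preterm to term by selenium. Selenium has no other effect.

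**Formula.** Term LBW on placebo is q. Term LBW on selenium is [(1 − pc)·q + (pc − pt)·r] / (1 − pt). This exceeds q exactly when pt < pc and r > q.

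**Base case:** pc = 25%, pt = 15%, q = 8%, r = 30%.

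- Placebo: 8.0%.
- Selenium: (0.75 × 0.08 + 0.10 × 0.30) / 0.85 = 0.090 / 0.85 = 10.6%.
- RR = 0.1059 / 0.08 = 1.32, with no baby harmed.

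**Range on the same base case (pc 25%, q 8%).** The ratio rises with both the preterm reduction and r, so the extremes are at the corners:

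| Preterm reduction | r | Term LBW on selenium | RR |
|---|---|---|---|
| 5 points | 25% | (0.06 + 0.05 × 0.25) / 0.80 = 9.1% | 1.13 |
| 20 points | 40% | (0.06 + 0.20 × 0.40) / 0.95 = 14.7% | 1.84 |

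**When the bias vanishes.**

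- No effect on preterm birth (pt = pc = 25%): 0.06 / 0.75 = 8.0%, RR 1.00.
- Equal risks (r = q = 8%): (0.06 + 0.10 × 0.08) / 0.85 = 8.0%, RR 1.00.

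**How much true growth benefit could be masked.** Keep r = 30% and let selenium also lower the LBW risk of the always-term babies to q′. Term LBW then equals the placebo value when (0.75·q′ + 0.03) / 0.85 = 0.08, so q′ = (0.068 − 0.03) / 0.75 = 5.1%. A true fall from 8% to 5.1% would show as no difference.

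**Counting term LBW events over all births instead.** Placebo: 0.75 × 0.08 = 6.0%. Selenium: 0.06 + 0.03 = 9.0%. RR = 1.50. The denominator is restored, but each baby moved to term can only add events.

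**LBW in all births.** Assume 60% LBW among preterm babies on placebo. Placebo: 0.25 × 0.60 + 0.75 × 0.08 = 21%. Let s be the LBW risk the shifted babies would have had if born preterm. Selenium is then 0.21 − 0.10 × (s − 0.30):

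- s = 60%: 18%
- s = 40%: 20%
- s = 30%: 21%

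**Numbers contributing.** With 20% drop-out, 90 × 0.80 = 72 women per arm. The term groups in the base case are 72 × 0.75 = 54 on placebo and 72 × 0.85 = 61 on selenium.

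**The case against.** Preterm birth and term LBW do not overlap, and together they separate prematurity from growth restriction. Term LBW is a coherent marker of growth restriction. An LBW preterm baby is not lost to the trial, because it already counts as an event in the first primary endpoint. All-birth LBW would repeat much of that endpoint: in the illustration 15 of the 21 placebo points (0.25 × 0.60) come from preterm babies. All of this stands. It supports reporting term LBW, but it does not make the term groups comparable as randomised.

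The base-case distortion is also small against sampling error. It corresponds to about 4.3 events among 54 term babies against 6.5 among 61. The 2.6-point gap is about half of one standard error: √(0.080 × 0.920/54 + 0.106 × 0.894/61) = 5.4 points. This too stands. In one trial of this size the bias would more often blur the result than produce a significant finding of harm.

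The wording of the aim could be introductory shorthand, with section 2.6 as the operative definition. That is possible, but the two still need to agree. An unseen analysis plan might count events over all randomised women, but the working shows that this does not remove the distortion. The logistic regression in section 2.8 adjusts for measured confounders and cannot be relied on to undo selection on an outcome.

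A reader might infer that the two primary endpoints necessarily work against each other, or that an effective supplement would look harmful. The documents do not support that. It requires an effect on preterm birth, a higher LBW risk in the shifted babies, and no offsetting gain in growth; the article gives no figure for any of these.

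**Conclusion.** The point holds as a defect in the definition of a primary endpoint. Two parts need no assumed rates: the term restriction selects on a post-randomisation outcome, which is at odds with the stated intention-to-treat principle, and the endpoint does not match the aim in the Introduction.

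The bias is conditional. It runs against selenium if selenium reduces preterm birth and shifted babies have a higher LBW risk than other term babies. It is absent by this route if selenium leaves preterm birth unchanged or if the risks are equal. Under the assumed base case the RR is 1.32, and across the stated ranges it is 1.13 to 1.84. These figures show what is possible and do not predict this trial's result.

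A reader might also infer that all-birth LBW would clearly show the benefit that term LBW hides. That does not follow either: the fall from 21% ranges from 3 points to none, depending on the LBW risk the shifted babies would have had if born preterm. The case for all-birth LBW is that it keeps the randomised comparison and matches the aim.

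**What to change.** In section 2.6, define the second primary endpoint as birth weight below 2.5 kg among all births to randomised women, whatever the gestational age at delivery, analysed by assigned arm.

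State a rule for pregnancies without a live birth, because a denominator of births is itself fixed after randomisation and mid-trimester miscarriage is a secondary endpoint. For example, include stillbirths by their birth weight, report miscarriages by arm, and add a sensitivity analysis that counts miscarriages as unfavourable outcomes.

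Keep LBW in term neonates as a descriptive secondary endpoint, with a note that it is not a comparison of the groups as randomised.

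No new data are needed for the main change: section 2.5.1 already records birth weight and gestational age at delivery. Section 3.1 says recruitment had not begun when the manuscript was first submitted. There are two costs. All-birth LBW overlaps substantially with preterm birth, so the two primary endpoints will be more strongly correlated. The change must also be entered in the trial registry and reported to the ethics committee, as section 2.5.1 requires for protocol modifications.
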